### Ethical Considerations

The study protocol has been approved by the ethics committee of Tabriz University (code IR.TABRIZU.REC.1402026). All data will remain confidential and only the researchers have access to the data. Initial examinations were performed by a specialist doctor in compliance with ethical protocols, and all entrance tests were conducted with the permission of the participants and in a completely confidential manner. All participants provide informed consent before inclusion, and it is explained to them that they can withdraw from the project at any time. The participants are also assured that their information will remain strictly confidential with the research group and that the study data are completely anonymous.

All medical tests, counseling and educational services, familiarization classes with the calorimeter, and other services are provided to the participants completely free of charge. We have also insured our gym for 1 year and all safety points are guaranteed. In particular, given the outbreak of viruses such as COVID-19 and influenza, we implemented all health protocols and repeatedly announced health principles to all athletes using the gym. Before starting the research project, all participants were examined by the research team’s specialist and underwent cardiovascular tests such as echocardiography, blood pressure control, blood oxygen, and sports performance tests. Finally, all participants were provided with insurance in the case of exercise-related injuries by the research team for 1 year.

### Blinding

During the data collection, physical fitness and blood tests as well as anthropometric measurements will be performed in the test center, and the laboratory analysts will not have information about the group allocation of the samples or participants.

### Intervention Fidelity

There are two instructors per class who will administer the intervention in all cases. At random intervals, an independent assessor will observe all classes and monitor them for content consistency using a checklist based on the explicit components of the exercise intervention protocol. In addition, instructors will maintain a log of activities in each class and these logs will also be reviewed by the independent assessor to confirm intervention fidelity.

### Sample Size and Group Allocation

The sample size was determined by a power calculation to detect group differences in the primary outcomes. Previous randomized controlled trials of exercise interventions have demonstrated effect sizes between 0.24 and 1.17 in similar populations for cognitive performance measures following aerobic interventions. To obtain 80% statistical power with an α level of .05, using an *F*-test for three independent groups and an effect size of 0.6, the sample size required was determined to be 30 participants using G*Power version 3.1. Among 60 applicants, a total of 33 participants have been recruited after primary evaluations, including height, weight, fat percentage, waist circumference, BMI, confirmation of the activities performed in the last year, and the lack of medical restriction to participate in the exercise training.

Following written informed consent of all participants and an explanation of the risks and benefits of the research, participants were randomized into the three groups: high-calorie-expenditure (n=11), standard-calorie-expenditure (n=11), and control (n=11) groups.

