**Objective:**

The aims of this research protocol are to (1) develop a high-calorie-expenditure training program to cover target calorie expenditure according to the trainability of women classified as overweight (according to a BMI of 25-29.9 kg/m^2^); (2) determine the effect of high-calorie-expenditure workouts on conditioning, glycemic variables, and body composition; and (3) evaluate the implementation of the intervention and results in comparison with outcomes obtained under a standard-calorie-expenditure training program.

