**Methods:**

This is a randomized controlled trial with a pretest-posttest design. Participants include 33 women with a BMI in the overweight range (25-29.9) allocated to three groups: two intervention groups and one control group. The intervention will be conducted for 12 weeks. Participants in the first group will be assigned an exercise program with high energy expenditure of approximately 3000-3500 kilocalories/week in the form of 5 sessions per week with an intensity of 50%-75% maximum oxygen rate (VO_2_ max) and 60%-80% target heart rate. The second group will be assigned an exercise program with a standard energy expenditure of approximately 1200-1500 kilocalories/week with 3 sessions per week at an intensity of 60%-75% VO_2_ max, according to The American College of Sports Medicine guideline. The effects of the multimodal training program with daily tasks will be compared to those of the standard-calorie-expenditure and control (no exercise) conditions with respect to changes in glycemic indices and body composition. Daily calories will be calculated through the International Physical Activity Questionnaire and using Nutrition 4 software.

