**Figure 1 figure1:**
[figure not shown]
Study design and a summary of the proposed 12-week training programs for the two intervention groups and the control group. CG: control group; HC: high-calorie-expediture exercise; SC: standard-calorie-expenditure exercise.

**Table 1 table1:** Schedule of tests and measures for the primary and secondary outcomes.

Tests	Week											
	1	2	3	4	5	6	7	8	9	10	11	12
Blood sample	✓											✓
Functional test	✓					✓						✓
Appetite	✓					✓						✓
Body composition	✓		✓			✓			✓			✓
Physical activity	✓	✓	✓	✓	✓	✓	✓	✓	✓	✓	✓	✓
Nutrition	✓	✓	✓	✓	✓	✓	✓	✓	✓	✓	✓	✓

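### The 80% power rests on effect sizes for cognitive performance, which the trial does not measure, so it is unsupported for body composition, glycemic or functional outcomes

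*Protocol article*

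**What the plan says.** The Sample Size and Group Allocation section of the protocol article opens with this purpose: "The sample size was determined by a power calculation to detect group differences in the primary outcomes". It then cites earlier exercise trials that found "effect sizes between 0.24 and 1.17 in similar populations for cognitive performance measures following aerobic interventions". The targets follow ("To obtain 80% statistical power with an α level of .05"), with an F-test "for three independent groups and an effect size of 0.6". The result is given as "an effect size of 0.6, the sample size required was determined to be 30 participants using G*Power version 3.1". Thirty-three women were randomized, 11 per group.

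The section does not say whether 0.6, or the cited range, is Cohen's f, a standardised mean difference or something else. It does not say how 0.6 was drawn from the range.

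The outcomes lie elsewhere. The Objective is to "determine the effect of high-calorie-expenditure workouts on conditioning, glycemic variables, and body composition". The abstract's Methods compare the groups "with respect to changes in glycemic indices and body composition". Table 1 ("Schedule of tests and measures for the primary and secondary outcomes") lists blood sample, functional test, appetite, body composition, physical activity and nutrition. The outcome sections add energy expenditure, perceived exertion, maximum oxygen, muscle tests, a metabolic syndrome score and an eating-attitude questionnaire. None is a cognitive test.

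**The concern.** The calculation claims to cover the primary outcomes, but the evidence for its key input comes from a different outcome domain. Article condensation does not explain this, because a justification is printed and it concerns something the trial does not measure. No expected difference or SD is given for weight, fat, glycemia or fitness, and no single outcome is labelled primary, so nothing else in the article supports the figure.

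This is the article's only power statement. Glycemic, inflammatory and blood analyses were still under way when it was written. A non-significant result there could be read as absence of a difference in a trial with 80% power, when the power for that outcome is unknown and may be low.

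**Working it through.** **Inputs from the article:** alpha 0.05, power 80%, three groups, effect size 0.6, required N = 30, randomized N = 33 (11 per group).

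**1. Reproducing the plan's figure.** For a one-way omnibus F-test the noncentrality is λ = N × f², with 2 and N − 3 degrees of freedom.
- N = 30, f = 0.6: λ = 30 × 0.36 = 10.8, critical F = 3.354, power = 0.8004.
- N = 27 gives 0.748. N = 33 (λ = 11.88) gives 0.843.

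The total of 30 is matched exactly. Other readings that enter 0.6 do not return 30:
- As a standardised mean difference d, it needs 126 to 165 (step 3).
- As f for the between-group effect with two time points and an assumed correlation of 0.5, it needs 24.
- As f for the time-by-group interaction under the same assumptions, it needs no more than 12.

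**2. What f = 0.6 means.**
- Variance explained: f²/(1 + f²) = 0.36/1.36 = 0.265.
- One arm differs from two equal arms: f = d√2/3, so d = 0.6 × 3/√2 = 1.27 SD.
- Equally spaced means: f = d/√6, so d = 0.6 × √6 = 1.47 SD.

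**3. Setting 0.6 against the cited range.** The metric is unknown, so both readings are shown.

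*Range in d (assumption).* The implied 1.27 to 1.47 SD exceeds the top value, 1.17. Unadjusted power at N = 33:

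| d | f (equally spaced / one arm differs) | power |
|---|---|---|
| 0.24 | 0.098 / 0.113 | 7% / 8% |
| 0.60 | 0.245 / 0.283 | 21% / 26% |
| 1.17 | 0.478 / 0.552 | 64% / 77% |

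For d = 0.6, 80% power would need 165 or 126 women.

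*Range in f.* Here 0.6 lies inside the range. The lower end, f = 0.24, gives 18% power at N = 30 and 20% at N = 33. The range would still describe cognition.

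**4. Effect of baseline adjustment.** With pre-post correlation r, f becomes f/√(1 − r²), with one fewer denominator degree of freedom. The article gives no r, so a range is assumed. For d = 0.6 in raw SD units at N = 33:
- r = 0.5: power 26% to 34%
- r = 0.8: power 50% to 63%
- r = 0.9: power 79% to 90%

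**5. What 33 women can detect, unadjusted, with 80% power.**
- Omnibus F-test: f = 0.568.
- A single pairwise comparison, 11 per group, pooled SD on 30 degrees of freedom, two-sided 0.05 without multiplicity correction: 1.23 SD.

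**The case against.** The strongest reply is that nothing was miscalculated. Cohen's f is the correct input for this F-test, 30 follows from it, and 80% power holds for any outcome whose true f is 0.6. That stands. A reader might infer that the stated power applies to no outcome of the trial, but power is conditional on the effect. The fault is that no evidence is given that any measured outcome has such an effect.

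A reader might also infer that a standardised mean difference of 0.6 was typed in as f. This is plausible, since f = 1.17 would mean 1.369/2.369 = 58% of variance explained, which is an odd top for a range of f values. The article names no metric, however, and the cited trials are not at hand, so the mix-up is not shown. An interaction test with f = 0.3, two time points and correlation 0.5 also gives 30, because its noncentrality is the same: N × 0.09 × 2/0.5 = 0.36N. The text describes a test of three independent groups with 0.6, so the one-way reading fits better. Either way the input rests on cognitive outcomes.

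A third inference, that the trial has only 21% to 26% power, is not supported. It needs the d reading and ignores the pretest-posttest design. Step 4 shows that adjustment could raise power a little or a great deal.

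Finally, the article already reports significant weight loss and a significant time-by-group interaction. Those results do not validate a planning assumption afterwards, and they say nothing about power for glycemic outcomes.

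**Conclusion.** The concern holds as a fault in the input to the calculation. The 80% figure is correct arithmetic for f = 0.6, but its only support is for cognitive performance, so it is unsupported for every outcome this trial measures. This conclusion needs no assumption about the metric of the cited range.

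The assumed effect is very large: 26% of variance explained, or 1.27 to 1.47 SD between the extreme groups. That it exceeds everything cited is conditional on the range being in d. The 21% to 26% power at d = 0.6 is conditional on that reading and on no baseline adjustment. Actual power for body composition or glycemia cannot be fixed from the article, because it gives no SD, expected difference or pre-post correlation.

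**What to change.** Rewrite the sample-size paragraph:

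- Delete the cognitive-performance justification.
- State that 0.6 is Cohen's f, confirmed against the G*Power output, and that it implies a largest pairwise difference of 1.27 to 1.47 SD.
- Present 33 as a fixed number. An unadjusted omnibus F-test has 80% power only at f of about 0.57 or more, and a single unadjusted pairwise comparison only at about 1.23 SD. Add that a baseline-adjusted analysis can detect smaller effects, by an amount that depends on the pre-post correlation.
- Report non-significant outcomes as estimates with confidence intervals, not as evidence of no difference.
- Do not name a primary outcome now. Weight, BMI, fat and muscle results are already reported, so choosing among them would be post hoc selection. Use only an outcome designated before the data were seen, for example in the registration if it names one. Otherwise say that none was pre-specified.

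The cost is one paragraph and a less favourable power statement. No participants are added, and allocation and conduct are unchanged.

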### Outcome Measures

#### Baseline Measures

Before starting the training, the participants undergo a 2-week familiarization period with the physical tests and training protocol. Participants’ anthropometric characteristics such as height, weight, and body composition variables (determined at 220 Hz with the device) are measured prior to randomization.

#### Physical Activity

The baseline physical activity of the participants will be assessed with the International Physical Activity Questionnaire (IPAQ) short form (7 items) and long form (IPAQ-L, 27 items) considering a reference period of the past 7 days. The IPAQ-L is a widely used tool that queries 5 activity domains independently and provides specific details on physical activity intensity levels, differentiating between usual weekdays and weekend days by measuring sitting time [20].

#### Calorie Expenditure

Apple Watch Series 6 (Apple Inc) was used to measure the energy expenditure in each exercise session. Apple Watch is an accelerometer-based device that provides estimates of heart rate, distance traveled, calories burned, minutes of activity, and standing time. When using the associated Workout app, the Apple Watch continuously measures heart rate during exercise, and the heart rate sensor is designed to compensate for low signal levels by increasing both the light-emitting diode brightness and the sampling rate. Calories burned represent both active calories and total calories. Energy expenditure during exercise will be determined based on the VO_2_ max measurement in milliliters and body weight, and thus evaluated according to each participant’s individual characteristics [22]. The Apple Watch was selected for all monitoring periods and all types of training. Raw data are exported to Microsoft Excel via Apple Health [23]. The Apple Watch monitors physical activity by entering and updating information such as height, weight, and wrist circumference, and then outputs the energy consumption of the exercise [22]. The Apple Watch data will be validated using the following formulas of the ACSM for females [24]:

Calories/minute = [–20.4022 + (0.4472 × heart rate) – (0.1263 × body weight in kg) + (0.074 × age)]/4.184

Calories burned per minute = (METs × 3.5 × body weight in kg)/200

In this formula, METs refers to metabolic equivalents as a measurement of exercise intensity, where 1 MET=3.5 mL/kg/min based on completion of the 3-min exercise stage, and METs=8.975–0.065 (age in years) [22]. The energy expenditure during the day and night is then computed as follows [25]. First, the activities performed over 24 hours are calculated to obtain the approximate energy consumption for different physical activities in relation to the resting energy expenditure (REE) [26]. The value is presented for activity per hour for a healthy body and sleep, where REE×1 indicates general activities, REE×1.5 indicates light activities, REE×5.2 indicates moderate activities, and REE×5 and REE×7 indicate heavy activities. Second, the activity factor is multiplied by the duration of the activity. Third, the energy consumption for REE and physical activity is calculated as the average activity factor×exercise period×REE. Finally, the total energy consumption is calculated by multiplying the number obtained in the previous step, which is equivalent to the thermal effect of food.

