### High-Calorie-Expenditure Training Protocol

Compared to the standard program, the exercise prescription for the high-calorie-expenditure group has a longer duration (45-110 vs 40-65 minutes per session), lower intensity (50%-75% vs 60%-85% VO_2_ max), and more frequent exercise (5 vs 3 times a week). Walking and running are the preferred forms of exercise to maximize calorie burning in comparison to weight training (cycling or rowing), which burns fewer calories. In the high-calorie-expenditure group, the goal of exercise expenditure is 3000-3500 kilocalories per week [30], which is achieved after 2-4 weeks of gradual lengthening of the exercise periods. The training protocol also lasts for 12 weeks, with 45 minutes of whole-body training at 65%-85% VO_2_ max consuming 1200 kilocalories per week; based on the principle of gradual overload with increasing weight, the energy expenditure at the end of the training period will be 3500 kilocalories. The calories increase per week [37] and the training time increases to 112 minutes. The main element of training is the same as that of the standard protocol, which starts with 3 sessions per week and gradually increases to 5 sessions per week, although the duration of each training session will be twice that for the standard-calorie-expenditure program in each step (Table 3).

In addition, the participants will be taught how to measure their heart rate in 10 seconds using the two index and middle fingers to find the pulse of the carotid artery of the neck and the pulse of the wrist. Participants will report their heart rate during aerobic exercise when requested by the investigator [38]. After 1 minute of active rest, each participant will begin a full-body exercise.

**Table 3 table3:** High-calorie-expenditure training protocol on a weekly and session basis (3 sessions/week).

Parameter			Week 1		Week 2		Week 3		Week 4		Week 5		Week 6		Week 7		Week 8		Week 9		Week 10		Week 11		Week 12
Total time (min)			135		135		150		150		246		280		340		340		475		525		530		530
EXE^a^ (min)			20		20		20		30		30		30		40		40		40		50		50		50
MHR^b^, %			65-75		70-85		65-75		70-85		65-75		70-85		65-75		70-85		65-75		70-85		65-75		70-85

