### Training Exercise or Multimodal Program for One Session

In both groups, participants report their weekly exercise with an exercise physiologist to estimate caloric intake and ensure compliance. After 1 minute of rest after completing the aerobic exercises, whole-body exercises are performed, consisting of 10 repetitions of the movement, in such a way as to replace the energy expenditure specified in the program and prevent repetition of the exercises. The body weight training pattern shows the energy expenditure during exercise, and the calories burned for the warm-up and cool-down periods are also calculated from the smartwatch and verified from the ACSM formula [39]. To avoid fatigue and repetition of movements during the training period, the movements are changed in a variety of ways every week, as shown in Figure 2.

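### The two equations said to validate the watch calories do not independently verify session energy expenditure: one is fixed by age and weight, the other probably reuses the watch's own heart rate

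*Protocol article*

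**What the plan says.** All of this is in the protocol article.

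- **Calorie Expenditure, the watch.** The watch is used for all monitoring periods and all types of training. On heart rate: "When using the associated Workout app, the Apple Watch continuously measures heart rate during exercise". It is called an accelerometer-based device, and it outputs exercise energy after height, weight and wrist circumference are entered. The section also says exercise energy will be determined from VO2 max and body weight, without saying how this relates to the watch.
- **Calorie Expenditure, the check.** "The Apple Watch data will be validated using the following formulas of the ACSM for females". One equation contains the term "0.4472 × heart rate" plus body weight and age. The other is "Calories burned per minute = (METs × 3.5 × body weight in kg)/200", with METs then set to 8.975 minus 0.065 times age.
- **Training Exercise or Multimodal Program for One Session.** Warm-up and cool-down calories "are also calculated from the smartwatch and verified from the ACSM formula".
- **High-Calorie-Expenditure Training Protocol.** Participants learn a 10-second pulse count. "Participants will report their heart rate during aerobic exercise when requested by the investigator". No link to the calorie check is stated.
- **Maximum Oxygen.** A gas analyzer is mentioned for maximum oxygen consumption, not for session calories.

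**The concern.** Weekly kilocalories define the exercise arms (3000 versus 1200 in Study Design). The Results state that the energy-expenditure goal was achieved, and the Discussion gives 800 kcal per session in the high arm as a watch estimate. The stated validation is the only support offered for those figures.

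A validation needs a comparator that follows what was done in the session and has errors separate from those of the device. One equation here does not follow the session at all. The other does so only through heart rate, and probably the watch's heart rate. At stake is the claim about delivered dose and the size of the dose contrast. The randomised comparison of outcomes does not use watch calories and is not affected.

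**Working it through.** The article gives no figure for watch error or agreement, so there is none to reproduce. Both equations can be evaluated as printed.

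**Inputs.** Ages 35 to 50 (Study Population). Late-week minutes: 530 (Table 3, weeks 11 and 12) and 190 (Table 2, weeks 9 to 12). Alternatives are 5 sessions × 110 min = 550 for the high arm (session length and frequency in the High-Calorie-Expenditure Training Protocol) and 3 × 80 = 240 for the standard arm (Study Design). Assumptions of this review: body weight 70 kg (range 65 to 80) and a heart-rate error of 10 beats/min.

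**MET equation.** At age 42.5, METs = 8.975 − 0.065 × 42.5 = 6.2125. Then 6.2125 × 3.5 × 70 / 200 = 7.61 kcal/min, or 4033 kcal over 530 min, at any heart rate. Over ages 35 to 50 and 65 to 80 kg the constant runs from 6.51 to 9.38 kcal/min.

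**Heart-rate equation.** kcal/min = (−20.4022 + 0.4472 × HR − 0.1263 × kg + 0.074 × age) / 4.184. At age 42.5 and 70 kg:

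| HR (beats/min) | Heart-rate equation (kcal/min) | MET equation (kcal/min) |
|---|---|---|
| 110 | 5.52 | 7.61 |
| 130 | 7.66 | 7.61 |
| 150 | 9.79 | 7.61 |

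True intensity alone therefore moves the heart-rate equation from about 27% below to 29% above the MET equation. A disagreement with the MET equation cannot be attributed to a heart-rate error.

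**Size of a shared heart-rate error.** The slope is 0.4472 / 4.184 = 0.1069 kcal/min per beat/min, so 10 beats/min is 1.07 kcal/min.

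- High arm: 1.0688 × 530 = 566 kcal/week.
- Standard arm: 1.0688 × 190 = 203 kcal/week.
- Shift in the contrast: 566 − 203 = 363 kcal/week.
- With 530 and 240 min: 1.0688 × 290 = 310. With 550 and 190 min: 1.0688 × 360 = 385.

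Against the nominal gap of 3000 − 1200 = 1800 kcal/week, 310 to 385 is 17% to 21%. An error of 5 beats/min halves these figures and one of 20 doubles them.

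**What palpation can resolve.** A 10-second count moves in steps of 6 beats/min, or 0.64 kcal/min (about 340 kcal over 530 min). Rounding alone has an SD of 6/√12 = 1.7 beats/min and averages down over repeated counts, so a mean bias near 10 beats/min could be seen. In week 12 of Table 3 the aerobic part is 50 min beside 60 min of whole-body work, so palpation during aerobic exercise leaves the larger part uncovered.

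**The case against.** A reader might infer that the check is fully circular, so that a heart-rate error can never be detected. The documents do not support that, and the case against it is sound:

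- Nothing says that watch heart rate enters the heart-rate equation.
- Nothing says that watch calories are computed from heart rate. The device is described as accelerometer-based. If its calories come mainly from movement, a heart-rate error would move the equation and not the watch, and a gap would appear.
- The MET equation has no heart-rate term, so an inflated watch value would move away from it.
- A manual pulse count exists that could reveal a gross error, although no such use is planned.

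It can also be said that the arms are fixed by sessions, minutes and intensity as well, that delivery is monitored by an independent assessor, class logs and perceived exertion, and that a condensed article may leave the heart-rate source to the full protocol.

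These points limit the claim but do not remove it. The article does state its validation method, and the MET equation is blind to session intensity on its face. Logs and perceived exertion do not measure kilocalories, and no measured criterion for session energy is described.

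**Conclusion.** The concern holds in limited form: the article claims a validation of session calories that the described comparison cannot provide. That the MET equation is constant for each woman follows from the printed formulas and needs no assumption. That the heart-rate equation shares the watch's input is probable, not stated.

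The figure of 363 kcal/week (310 to 385) is illustrative. It rests on three assumptions: watch heart rate feeds the equation, watch calories depend on the same heart rate, and a 10 beats/min error runs in the same direction through every minute in both arms. Under these, the check as described would not reliably show the error; to say that it could not show it would go too far. The point should be corrected because it bears on what can be claimed about delivered dose. It does not threaten the randomised comparison.

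**What to change.** 1. State which heart rate enters the heart-rate equation.
2. Do not use the age-only MET value as a check on session calories.
3. Where palpated pulse is already reported, compare it with watch heart rate at the same moments during aerobic work, as a spot check.
4. Report the watch-minus-equation mean difference and limits of agreement by arm and training phase.
5. Call the comparison a cross-check, and describe delivered kilocalories as watch-estimated, not validated.
6. Reconcile the session durations in the text and tables, since the weekly totals depend on them.

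The cost is small: wording, and a short agreement summary from data largely in hand. The spot check is coarse. It resolves 6 beats/min per count, covers only aerobic work, and is described only for the high arm, so any comparison between arms would need the standard arm to record pulse as well. The claim about achieved dose becomes more modest.
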